#### Intervention implementation

The intervention will be delivered into practices remotely over the EMIS Web system, and then activated on day 1 of the trial. Participant practices will receive information about the intervention from the study team prior to the study. This is a pragmatic trial, in which we will test the electronic intervention in routine practice. Intervention practices will agree to invite all patients on the list produced by the tool at the start of the trial, excluding those clearly unsuitable, for a consultation to discuss OAC therapy. The invitations will include an information sheet, provided by the study team, which gives patients details about AF and anticoagulation. Invitations will be sent within the first week of the trial, with reminders to non-attendees after one month.

Additionally, from day 1 of the trial screen reminders will appear in the medical records of eligible patients. Both the lists and screen reminders aim simply to promote current UK guidelines, and not novel management of AF [19].

### Control practices

Control practices will continue with usual care, which as of April 2012 included requirements placed on practices by the Quality and Outcomes Framework (QOF) [20]. The control practices will have the trial software installed, but this will run in a non-active format. There will be no eligible list generated and no screen reminders. The software will record the number of patients eligible for anticoagulation, the number receiving treatment and other secondary study outcomes throughout the trial.

### Study outcomes

#### Primary outcome

The primary outcome will be the proportion of patients with diagnosed AF, and eligible for anticoagulation under recent guidelines (NICE TA249) [19], who are prescribed therapy 6 months after the start of the intervention.

#### Secondary outcomes

Secondary outcomes include the following:

1. The proportion of patients with CHADS_2_ score ≥2 prescribed anticoagulants. CHADS_2_ is a commonly used scoring system for stroke risk in atrial fibrillation [8].

2. A record of inappropriate care or prescribing related to anticoagulation in patients with AF.

3. The incidence of stroke, transient ischaemic attack (TIA), or other major thromboembolism during the trial, in patients with AF eligible for OAC.

4. The incidence of major haemorrhage during the trial in patients with AF eligible for OAC.

The denominator for the primary outcome will be all of those eligible for OAC therapy at the end of the 6-month trial period. This will include those whose eligibility has arisen since the start of the trial, for instance through reaching the 65- or 75-year age thresholds, or through a new diagnosis of a condition relevant to eligibility. It is important that the size of the denominator population is not influenced by use of the tool, as this could lead to ascertainment bias. We will therefore exclude from the outcome denominator those whose eligibility has arisen during the study purely as a result of improved recognition of diabetes, hypertension, heart failure, or thromboembolic stroke by the AURAS-AF tool, as the control arm will not be influenced by this improved recognition (see ‘Intervention’ section above). This group will be identifiable through the recording of responses to screen prompts. Patients diagnosed with these conditions independently of the tool will not be excluded. Similarly, cases where an ‘Atrial Fibrillation Resolved’ code is applied (effectively removing the patient from the study population) will be retained in the denominator if this decision resulted directly from the use of the AURAS-AF tool in the intervention arm.

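### The month-6 primary denominator is corrected for the tool's influence in the intervention arm only; the correction is incomplete and leaves a risk of bias of unknown sign and probably modest size

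*Protocol article*

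**What the plan says.** The Primary outcome section of the protocol article takes the TA249-eligible patients with AF and asks what proportion there are "who are prescribed therapy 6 months after the start of the intervention". The denominator is defined later, in the paragraph that closes Secondary outcomes: "The denominator for the primary outcome will be all of those eligible for OAC therapy at the end of the 6-month trial period". It is not a cohort fixed at baseline: "This will include those whose eligibility has arisen since the start of the trial", whether by age or by a new diagnosis.

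The article gives its reason for going further: "It is important that the size of the denominator population is not influenced by use of the tool, as this could lead to ascertainment bias". Two rules follow.

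- **Exclusion.** "We will therefore exclude from the outcome denominator those whose eligibility has arisen during the study purely as a result of improved recognition". The conditions concerned, when the tool picks them up, are thromboembolic stroke, heart failure, hypertension and diabetes. On how these patients are found: "This group will be identifiable through the recording of responses to screen prompts". Diagnoses made independently of the tool stay in.
- **Retention.** Patients given an AF-resolved code "will be retained in the denominator if this decision resulted directly from the use of the AURAS-AF tool in the intervention arm".

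Under Control practices, the software is installed but inactive. It counts eligible and treated patients, with no list and no reminders. Under Statistical analyses, practice-level proportions are compared by ANCOVA adjusted for baseline.

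**The concern.** The article sets its own test, that the tool should not influence the denominator. The two rules meet that test only if every excluded patient would have stayed uncoded without the tool, and every retained patient would have kept an active AF code without it.

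Neither can be observed. The words *purely* and *directly* call for a judgement about what would have happened otherwise. That judgement is made in one arm, by or about practices that know they are using the tool, with nothing equivalent in control practices.

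Two kinds of patient are then handled differently by arm. Some would have been coded by usual care within the 6 months, but the tool prompts first: they are logged as tool-recognised and dropped, while their control counterparts are counted. Others would have had their AF coded as resolved anyway: they may be kept in the intervention arm and lost from the control arm. If their treatment rates differ from the rest, the two proportions differ with no change in prescribing. ANCOVA on the baseline proportion cannot repair this, because the difference arises after randomisation and in one arm.

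**Working it through.** **The plan's own figures.** No figure is given for the denominator rules. The yardstick is the Sample size calculation: 53% rising to 66%, a 13-point difference. A two-proportion formula (5% two-sided, 95% power) gives 736 patients with 66% and 708 with the unrounded 66.25%, against the stated 720. Design effect: 1 + ((1 + 0.6²) × 54 − 1) × 0.03 = 3.17. Then 720 × 3.17 = 2,282; 2,282 / 54 ≈ 42.3 practices; × 1.1 ≈ 46.5, against 46 stated. The figures reproduce. They refer to the CHADS2 ≥2 group; I assume that 53% carries over to the TA249 group.

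**Assumed inputs (none is in the documents).**
- f: share of the month-6 denominator newly coded by usual care.
- g: share of those whom the tool reaches first.
- r: retained AF-resolved cases that usual care would also have removed, relative to the denominator.
- q: anticoagulation rate in the affected patients.

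Throughout, p = 0.53 and the tool has no true effect on prescribing.

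**Exclusion rule.** Control proportion: C = (1 − f)p + fq. Intervention proportion: I = [(1 − f)p + f(1 − g)q] / (1 − fg). The bias is I − C, which simplifies to fg(1 − f)(p − q) / (1 − fg), so its sign is that of p − q.

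Worked case, f = 2%, g = 50%, q = 0.30: C = 0.5194 + 0.0060 = 0.5254; I = (0.5194 + 0.0030) / 0.99 = 0.5277; bias +0.23 points.

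| f | g | q | Bias (points) |
|---|---|---|---|
| 1% | 25% | 0.30 | +0.06 |
| 2% | 50% | 0.30 | +0.23 |
| 5% | 100% | 0.10 | +2.15 |
| 5% | 100% | 0.53 | 0 |
| 5% | 100% | 0.70 | −0.85 |

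**Retention rule.** Bias = (p + rq)/(1 + r) − p = r(q − p)/(1 + r).
- r = 0.5%, q = 0.30: 0.005 × (−0.23) / 1.005 = −0.11 points.
- r = 2%, q = 0: 0.02 × (−0.53) / 1.02 = −1.04 points.

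**Together.** Taken one at a time, the rules leave about −1.0 to +2.2 points. They roughly add. With low treatment rates in both groups they offset; the extreme corners are about −0.85 − 1.04 = −1.9 and +2.15 − 0.11 = +2.0.

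**Without the rules, same month-6 denominator.**
- Extra tool-recognised patients, share h: bias = h(q − p)/(1 + h). For h = 5%, q = 0.30 this is −1.1 points; for h = 10%, q = 0.10 it is −3.9.
- Unretained tool-driven AF-resolved cases, share r: bias = r(p − q)/(1 − r). For r = 1%, q = 0.30 this is +0.23 points; for r = 5%, q = 0 it is +2.8.

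**With one pre-activation rule in both arms.** Neither mechanism can operate, so the bias from both is 0 by construction.

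**The case against.** The strongest reply is that the one-sided influence is the tool, and the rules are a declared repair. The article names the ascertainment bias and says why the repair applies to one arm. Mirroring the rules in control practices would have nothing to act on, and dropping them could leave up to about 4 points under the assumptions above. This stands: the rules are probably better than none.

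The exclusion is also narrow. Under the TA249 criteria as listed, recognising diabetes or hypertension changes eligibility only at ages 65 to 74 with no other criterion, and heart failure or stroke only below 75 with no other criterion. This favours the smaller values of f. Including new diagnoses is a deliberate choice of population, and supporting analyses may sit in the full protocol. Neither reply removes the mechanism in the definition as published.

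Stronger readings are tempting, but the documents do not support them.

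- *The effect is biased upwards.* The sign depends on treatment rates that the documents do not give, and the retention rule tends to push the other way.
- *Untreated patients leak out through the start-of-trial list review.* Practices agree to "invite all patients on the list produced by the tool at the start of the trial, excluding those clearly unsuitable", but that governs who is invited, not who is counted. The list is one of the tool's two components (Intervention), so AF-resolved codes prompted by it fall within the retention rule. The sentence on screen-prompt responses describes the exclusion group only. Statistical analyses promises reasons for patients not invited.
- *Type I error rises to 11%.* If 10% of untreated patients left unlogged, the proportion would rise by 0.53/(1 − 0.047) − 0.53 = 2.6 points. With a standard error near 3.7 points, √[(0.53 × 0.47 + 0.66 × 0.34) × 3.173 / (20.7 × 54)], that gives about 11%; a 5% loss gives 1.3 points and about 6%. The standard error for the primary outcome may well be smaller, but the loss rates themselves have no source.
- *Strokes clarified as haemorrhagic drop out with no restoring rule.* This requires unclarified stroke codes to have counted as eligible. The text does not say so, and its reference to eligibility arising on recognition of thromboembolic stroke suggests otherwise.

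**Conclusion.** The point holds as a risk of bias. The primary denominator is assessed after the tool has acted, and its correction rests on attributions that can be made only in the intervention arm. The correction therefore falls short of the article's own aim. On the assumed inputs the residual is about −1 to +2 points for either rule alone, with +0.06 to +0.23 in the milder cases for the exclusion rule. That is modest beside 13 points, though it would weigh more against a smaller true effect. The sign is not known, and the size rests on assumed f, g, r and q and on 53% applying to the TA249 group. This is a worthwhile and cheap improvement; it does not show that the planned comparison is invalid.

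**What to change.** Add an analysis, preferably as the primary and at minimum as a prespecified sensitivity analysis, with one denominator rule for both arms:

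- patients with AF who are TA249-eligible on codes entered before activation (by entry date);
- plus those who reach the 65- or 75-year threshold by month 6, on codes entered before activation;
- ignoring any AF-resolved or reclassification code entered after activation.

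Keep the present end-of-period definition as the companion analysis, and report by practice the numbers excluded and retained under its two rules, so that a reader can judge how much they matter.

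The cost is one rewritten paragraph, an entry-date filter in the search and one extra analysis. The software already counts eligible patients in control practices; I assume that the search can filter on entry date. Because the team receives outcome data aggregated to practice level (Ethical considerations), the filter has to be built in before extraction.

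The downside is that patients newly diagnosed with AF or a qualifying condition during the 6 months count only in the companion analysis, and genuinely resolved AF stays in the denominator of both arms.

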### Allocation

The 46 EMIS Web practices that consent to participate will be randomised into two equal groups (intervention and control). We will use balanced allocation due to the small number of practices. An independent statistician will randomise practices using block randomisation, stratifying for practice list size and the proportion of their eligible population prescribed OACs (groups separated by the median).

### Data collection

The primary data collection will use the capabilities of EMIS Web. The research team will enter into data sharing agreements with practices allowing us to securely access anonymous outcome data over an N3 NHS (secure) internet connection. Proportions of patients prescribed OACs, and incidence of stroke, TIA, other major thromboembolism and major haemorrhage in the TA249 eligible sample will be collected in this way. We will collect these outcomes at baseline, 3 months into the trial (for the data monitoring committee), at 6 months (at the end of the intervention phase) and after 12 months (see Additional file 1).

We shall additionally ask practices - both intervention and control - to fill in *pro forma* providing further information on strokes, TIAs, other major thromboembolisms and major haemorrhages. The number of these required from each individual practice is expected to be small. These will include information about the anticoagulation status (including international normalised ratio if available) at the time of the event and duration on therapy. The *pro forma* data will help to attribute outcome events to decisions around prescribing and the possible influence of the AURAS-AF software on these decisions. Intervention practices will also be asked to complete *pro forma* providing details of patients’ contact with the practice during the study that is relevant to anticoagulation. This will include responses to the initial invitation to consultation, and reasons behind decisions over therapy where discussions occurred. The main outcome data will be extracted immediately following the intervention phase, including the *pro forma*, with a second extract after a further 6 months. Finally, we ask practices to report any inappropriate care or prescribing in the AF population to the study team within one week of its occurrence.

#### Statistical analyses

We will compare baseline characteristics of randomised practices and their demographic characteristics between trial arms. For all randomised practices, we will report the aggregated number of eligible people identified at the start of the study, the proportion of these invited (with reasons if not invited), the proportion of attendees, and the proportion of those attending that commence anticoagulation by the end of the trial.

The anonymous data on anticoagulant prescribing from each practice will be aggregated and analysed using analysis of covariance (ANCOVA). We shall compare proportions of eligible patients who are using anticoagulation after 6 months, between intervention and control arms (primary outcome), adjusting for baseline values. We shall also compare this measure using data from one year after the start of the study. We will assess whether any practice characteristics have an impact on the intervention effect using multivariable regression. Incidence rates of stroke, TIA, other major thromboembolisms and major haemorrhage (secondary outcomes) will be compared between arms [23].

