### Sample size calculation

We have powered the study to detect changes in one of the secondary outcomes - change in proportion with CHADS_2_ score ≥2 who are prescribed anticoagulants. This is a smaller group than the denominator for the primary outcome, hence the need for greater power, but is important given its prominence in the QOF. We estimate a sample of 46 practices will be needed for the trial, accounting for clustering, variation in cluster size and 10 percent withdrawals [24]. This will give 95 percent power to detect a relative difference of 25 percent in proportion of eligible people who are treated between the trial arms, at 5 percent significance level.

The cluster size (*m* - number of patients with CHADS_2_ ≥2 in each practice) is estimated at 54 (based on mean list size and AF prevalence in the QOF [25], and recent CHADS_2_ estimates [8]). There is no relevant estimate of minimum change due to intervention; therefore we assumed 25 percent relative increase based on preliminary discussions. We estimated baseline prescribing of 53 percent [8], therefore 66 percent at follow-up. Assuming an intra-class correlation coefficient (ICC) of 0.03 (using a published ICC for inappropriate prescribing in the elderly [26]) and coefficient of variation (*cv*) of cluster size of 0.6 (based on a sample of THIN data on file; mean AF patients per practice = 119, standard deviation = 72) we estimate the design effect to be 3.17 (1 + ((1 + *cv*[2]) *m* - 1) x ICC) [27]. The initial total sample size, ignoring clustering is 720 (total in both arms) [28], therefore 2,282 accounting for the design effect. Including a 10 percent withdrawal this equates to 46 practices.

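### Randomisation is stratified by practice list size, but the stated primary ANCOVA adjusts only for baseline values; adding the list-size stratum is a cheap, modest gain in precision

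*Protocol article*

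**What the plan says.** Under Allocation, the 46 practices are block randomised in two equal groups, "stratifying for practice list size and the proportion of their eligible population prescribed OACs (groups separated by the median"). Under Statistical analyses, "The anonymous data on anticoagulant prescribing from each practice will be aggregated and analysed using analysis of covariance (ANCOVA"). The comparison at 6 months is made "between intervention and control arms (primary outcome), adjusting for baseline values". No other covariate is named for this model. The same section plans a multivariable regression, but that asks whether practice characteristics change the intervention effect. It does not put list size into the primary comparison.

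Two other places bear on the point. Ethical considerations says that the team receives only anonymised pro forma data or practice-level aggregates. Sample size calculation assumes that cluster size varies with a coefficient of variation of 0.6. Nothing in the article states or excludes weights for the practices.

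**The concern.** Stratified allocation balances list size between the arms. If list size also predicts anticoagulant prescribing, the between-arm difference is less variable than under simple randomisation. A model without list size leaves that variation in the residual, so it reports a standard error larger than the true one. The confidence interval is then wider than it needs to be, and the test rejects a true null less often than its nominal level.

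The team chose list size as one of only two stratifiers, so it presumably thought the factor mattered, and the usual practice is to analyse by the factors used to randomise. What is at stake is precision with 46 units, not bias.

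**Working it through.** **1. The plan's own figure.** Inputs from Sample size calculation: "This will give 95 percent power to detect a relative difference of 25 percent", "at 5 percent significance level" (two-sided assumed); "We estimated baseline prescribing of 53 percent [8], therefore 66 percent at follow-up" (0.53 × 1.25 = 0.6625 unrounded); a cluster size that "is estimated at 54 (based on mean list size and AF prevalence in the QOF"; "Assuming an intra-class correlation coefficient (ICC) of 0.03"; coefficient of variation 0.6.

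- N ignoring clustering, pooled two-proportion formula: 708 (for 0.6625) or 736 (for 0.66). The stated 720 lies between them.
- Design effect: 1 + ((1 + 0.36) × 54 − 1) × 0.03 = 1 + 72.44 × 0.03 = 3.17, as stated.
- 720 × 3.17 = 2,282, as stated. 2,282 / 54 = 42.3 practices; with 10% withdrawal this is 46.5 (× 1.1) or 47.0 (÷ 0.9), against 46 stated.
- Power with 46 × 0.9 = 41.4 practices: 41.4 × 54 / 3.173 = 705 effective patients, which gives 94.9% (for 0.6625) or 94.2% (for 0.66).

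The calculation reproduces. It takes no credit for baseline adjustment or for list size.

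**2. Leaving out list size.** Let r be the partial correlation of list size with the 6-month practice proportion, given arm and baseline. Adding list size multiplies the standard error by √(1 − r²). The documents give no value of r, so it is varied as an assumption. Power uses the planned design effect and 41.4 practices.

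| Assumed r | √(1 − r²) | SE too large without list size | Power with list size added |
|---|---|---|---|
| 0 | 1.000 | 0% | 94.9% |
| 0.1 | 0.995 | 0.5% | 95.1% |
| 0.2 | 0.980 | 2.1% | 95.7% |
| 0.3 | 0.954 | 4.8% | 96.5% |
| 0.5 | 0.866 | 15.5% | 98.6% |

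The formula treats list size as a continuous covariate. A median split captures only part of it, so these are upper figures for the stratum indicator.

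**3. Simulation.** Settings: 46 or 42 practices, 4,000 runs each, correlation 0.6 assumed between baseline and follow-up practice effects, and a list-size effect of zero or one of two assumed non-zero strengths.

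- Type I error of the baseline-adjusted ANCOVA without list size was 4.2–4.8%. With the stratum added it was about 4.4–5.1%. The simulation error at 5% is √(0.05 × 0.95 / 4,000) = 0.3 points.
- At the planned difference of 0.1325, adding the stratum changed power by −0.1 to +0.6 points.
- At a smaller difference of 0.08, the change was −0.5 to +2.3 points; the losses arose only when list size had no effect.

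**4. Weighting.** The variance of a practice proportion is proportional to ICC + (1 − ICC)/m. With equal weights, the design effect is m̄ × ICC + (1 − ICC) × m̄ × E(1/m). For lognormal sizes, m̄ × E(1/m) = 1 + 0.36, so the design effect is 54 × 0.03 + 0.97 × 1.36 = 1.62 + 1.32 = 2.94. For gamma sizes with a minimum of 5 patients it is 3.11 numerically, and with no minimum 1.62 + 0.97 × 1.5625 = 3.14. All are at or below the planned 3.17. Inverse-variance weights give 2.78 (lognormal) and 2.82 (gamma).

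The standard-error cost of equal weights at m = 54 is √(2.94/2.78) = 1.03 to √(3.11/2.82) = 1.05. But 54 is the CHADS2 ≥2 group, which the article says is smaller than the primary denominator. At assumed primary denominators of 80–119 the efficiency of equal weights is 0.93–0.98, a cost of about 1–4%.

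**The case against.** The strongest reply is that this is one unnamed covariate in a condensed article. The stratifier most clearly tied to the outcome, baseline prescribing, is already in the model in continuous form. No passage says that list size predicts prescribing, so the gain may be nil, and simulated power at the planned effect barely moves. All of that stands, and it limits the point to a modest one. It does not remove it: the article states the model and its adjustment, and list size is not in it.

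Three stronger readings are tempting, and the document does not support them:

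- **That small practices will count as much as large ones.** The article neither states nor excludes weights, and such detail may sit in the full protocol or SAP.
- **That precision already paid for is being lost.** The sample size allowed a design effect of 3.17. Even an equally weighted practice-level analysis needs only about 2.9–3.1, so the planned power holds.
- **That aggregation is a fault.** It follows from the data the team is permitted to receive. A practice-level comparison is also a standard, valid analysis when the practice is the unit of allocation.

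**Conclusion.** The point holds in a limited form. A factor used to stratify the randomisation is left out of the stated primary model. The consequence is possible conservatism: no bias, no excess type I error and no erosion of planned power. The standard error is too large by about 2% if the partial correlation of list size with the outcome is 0.2 and about 5% if it is 0.3. There is no loss if list size is not prognostic. Those correlations are assumptions. The simulated results also rest on the assumed 0.6 correlation between baseline and follow-up practice effects.

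The weighting question is secondary. Its size depends on the ICC: 0.03 is the plan's figure, borrowed from a different prescribing outcome. At an ICC of 0.01 and 54 patients per practice, the efficiency of equal weights would fall to 0.80–0.87; at higher ICCs it rises.

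**What to change.** State the primary model as the 6-month practice proportion regressed on arm, the baseline proportion (continuous) and the list-size stratum used at randomisation. Use the same covariates for the CHADS2 ≥2 outcome and the 12-month comparison, with each outcome's own baseline proportion. Fix this before outcome data are seen by arm.

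State also which weighting applies. If equal weights are kept, an analysis weighted by m / (1 + (m − 1) × ICC), with each practice's own denominator, can serve as a sensitivity analysis. If the intervention effect varies with practice size, weighting also changes the quantity estimated, so the choice should be deliberate. A logistic mixed model is not an interchangeable substitute, because it estimates a conditional odds ratio and not a difference in practice proportions.

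The cost is a sentence of text and one degree of freedom: 46 − 3 = 43 becomes 42 if all practices are retained. List size is known at randomisation, and the trial software already records the numbers eligible and treated, so no new data are needed.
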